### Primary study endpoint

The primary study endpoint is the wish for vaccine advice before the first recommended period of vaccination, which is related to the initial attitude/hesitancy toward vaccinations.

### Secondary study endpoints

Secondary endpoints are the description of the scope of vaccination advice (such as advice received on the vaccination date, self-informed, informed by a doctor during a checkup, or at a special appointment); the perceived direction of the advice (e.g., non-hesitant or hesitant or undefined regarding vaccination); and the identification of influencing factors and suggestions for improvement. In addition, the need for information among four groups of parents will be described, along with the information content (Figure 1):

(a) Non-hesitant to vaccination and immunized child at 12 weeks of age(b) Non-hesitant to vaccination but not immunized child at 12 weeks of age(c) Hesitant to vaccination and not immunized child at 12 weeks of age(d) Hesitant to vaccination but immunized child at 12 weeks of age.

**Figure 1 fig1:**
[figure not shown]
Schedule of shared decision-making and hence possible analyses of groups of new parents according to their attitude toward vaccination and actual action.

### Sample size calculation

The sample size calculation is based on the data from the Federal Center for Health Education (BZgA) (22) in Germany. According to a cross-sectional survey conducted by the BZgA involving parents with children of various ages (n = 1.153), parents who (tend to) reject vaccinations want less often more information (4%) than parents who (tend to) support vaccinations (25%), which corresponds to an odds ratio of 8. The survey reports that 7% of parents are hesitant and tend to reject vaccination.

Based on these assumptions, and calculated using a Fisher’s exact test with a power of 80% and a two-tailed significance level of 5%, a minimum of 378 parents is needed, with 28 (7%) of them identified as hesitant. Considering the possibility that some surveys could be incomplete, at least 400 parents are needed.

### Study duration

The recruiting period for key persons and families is set for 2 years until the end of 2025 but may be extended depending on the success of the recruitment strategies of this group, which can be difficult to reach because of their vulnerable life stage.

### Analysis plan

After sample size completion, two groups (hesitant versus non-hesitant) will be made based on their initial attitude toward vaccination assessed using the C7C questionnaire. Using a chi-square test, the primary research question, as to whether hesitant people have a lesser proportion of wish for vaccine advice, can be answered in a confirmatory and prospective way for new parents. All other secondary analyses are explorative. With regression analyses, we will try to explore the various attitudes and reasons for both vaccination and vaccine advice. Further secondary endpoints such as results of information content, trustworthiness of information of different professions, the perceived influence, and suggestions for improvement will be reported as descriptive statistics and divided by the four groups (hesitant and not vaccinated, hesitant and vaccinated, non-hesitant and not vaccinated, and non-hesitant and vaccinated) as described above. All details are defined in a statistical analysis plan prior to the analyses.

### Dealing with bias and limitations

In contrast to existing surveys regarding vaccination attitudes, this study prospectively investigates attitude, change of attitude, and actual implementation of vaccination in the most important age group for this topic, namely, parents of newborns. As the first vaccination is recommended within a few weeks after birth, the examination of new parents poses some difficulties. For example, parents may not be willing to take part in a study during the probably stressful period following a birth. Furthermore, one group of parents (e.g., vaccine-hesitant or non-vaccine-hesitant) could participate more. Therefore, we assess the vaccination attitude of the parents in the beginning to adjust the group size if necessary.

Based on the chosen study period, attrition bias is possible if families do not answer the second questionnaire after vaccination. Nevertheless, the intentions and wishes they offered in the first questionnaire will be mentioned in the analysis of the primary outcome. Parents are only included if they have answered the first survey completely. Drop-out rates can be evaluated exploratorily according to the parents’ intentions.

To reduce detection bias, the groups and the statisticians will be blinded toward the outcomes as described before.

One limitation of the study is the exclusive view of the parents without considering the influence of the physicians. This may be a strength, too, because parents could be more open, but further studies that address physicians’ viewpoints will be necessary. This study does, however, also assess the attitudes of the participating physicians using a modified version of the 7C questionaire (23). Depending on the findings of this exclusively observational design, further studies that include interventions may follow. The exclusively observational design reduces self-reporting bias because only the parents’ viewpoints are considered. Vaccination uptake will be reported by the parents, and this carries a risk of bias. This risk will be reduced by the detailed query of vaccinations, which asks for the date, vaccine name, and diseases against which vaccinations are given.

Furthermore, the parents may feel under pressure to answer the questionnaires and may answer incorrectly. This risk of bias primarily affects the secondary endpoints and can be addressed by including the timing of responses in the analysis. As in this first stage of life, many vaccination dates are recommended, and rapid response from the parents is necessary. However, parents may forget to answer because of lack of sleep or other difficulties associated with the first months of an infant’s life, so reminding can be helpful to keep the participation rate high.

As some parents may visit different offices and physicians with different attitudes toward vaccination, the study may have to deal with performance bias. To enhance external validity in this context, physicians are requested to register their offices, while parents are asked to document their treating physicians.

In addition to the parental attitudes, this study also investigates the vaccine advice received, from the parental perspective, and the actual vaccinations given. Therefore, unconsidered covariates could be investigated.

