### Data collection

The registration process and consent to participation for parents should end before the infant gets its first immunization, which is according to the immunization schedule as soon as the infant is 6 weeks old. Registration must take place before the child has passed the age of 8 weeks, as this is the recommended time frame of the six-fold vaccination, which is sometimes given together with the rotavirus vaccine, which is recommended from 6 weeks on.

After registration, parents receive emails with further information depending on the age of the infant. Parents of unborn babies indicate the expected date of birth. They receive an email asking them to state the actual date of birth 3 weeks after this date. Parents of babies already born get invited to answer the first questionnaire as soon as their baby is 6 weeks old. The electronic case report forms will be stored in the Research Electronic Data Capture (REDCap) system (19, 20). Before the first question, parents get informed about the use and security of their data and their option to withdraw their consent to the use of their data. The first questionnaire in which parents get asked for their personal data, such as names and addresses, is kept in a database that is separate from the child’s health questions. A link between both databases is only possible via record linkage, with the email address being essential for sending invitation emails.

Parents will be interviewed via online case report forms at two time points. The first is before the first recommended vaccination, as mentioned before. The second time point occurs when the infant is 12 weeks old, as this is the time when the recommended time slot for the first immunization is over (Table 1). By this time, parents will have made decisions regarding whether and how to immunize their infant. If parents do not answer a questionnaire, they receive up to five reminder emails, which are sent every 5 days.

**Table 1 tab1:** Invitation and visit schedule of INFORMed study.

Separate visits	(V-1)	(V0)	V1	V2
Age of observed child (months)	Unborn*	<1 ½*	1 ½*	3
Informed consent	X	X	X	
True date of birth		X		
Attitude toward vaccination (C7C), demographic data, health status of the parents and siblings, and their vaccination			X	
Type of information, source of vaccination information, influencing factors, and trustworthiness of information sources			X	X
Details about vaccination advice and vaccination status				X

*Registration possible.

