### Measurements

The main question of this study is if vaccine-hesitant parents with negative attitudes wish less vaccine advice, as reported. To elaborate this further, we evaluate if and what kind of vaccination advice has been given to the parents and what was missing in their opinion. To analyze the type of vaccination advice, the case report form at the first visit includes questions about:

The attitude toward vaccination will be assessed at the first visit using the C7C Scale (21). At the same time, confounding factors such as demographic data, health status of the parents and siblings, their vaccination status, and experience with vaccination will be assessed.Type of information based on a qualitative study (2) (e.g., effect and side effects, incidence and severity of the disease being vaccinated against, and information on divergent strategies)Source of vaccine information (Internet, books, circle of friends, midwife, and non-medical practitioner)Previous concrete understanding of the vaccination advice and strategyInfluence of professionals and of the social environmentTrust in professionals, social environment, and possible counseling centers

The second case report form at the age of 12 weeks (visit 2) contains the same questions, except the attitude toward vaccination but supplemented by information on:

The professional who gave the advice (e.g., pediatrician, general doctor, and additional or other specialties)Details about vaccination advice (separate appointment/in the context of prevention examination/only at the vaccination procedure/information by a counseling interview/in writing; which brochures were delivered, duration of vaccination advice, fulfillment of the parental expectations, change of vaccination decision by the advice given and in what way, and influence of vaccination decision on further medical care)Other sources of information (e.g., Internet, books, circle of friends, midwife, and non-medical practitioner)The actual action: vaccination status at 12 weeks.

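### Inclusion requires a fully completed first survey, although the primary test uses only the C7C grouping and the wish for advice, so usable parents may be dropped

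*Protocol article*

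**What the plan says.** All references are to the protocol article.

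- **Dealing with bias and limitations** sets the rule: "Parents are only included if they have answered the first survey completely". The sentence before it says that parents who miss the second questionnaire still contribute their first-visit answers to the primary outcome.
- **Primary study endpoint**: "The primary study endpoint is the wish for vaccine advice before the first recommended period of vaccination", related to initial attitude.
- **Analysis plan** forms the comparison groups: "two groups (hesitant versus non-hesitant) will be made based on their initial attitude toward vaccination assessed using the C7C questionnaire". It then names the test: "Using a chi-square test, the primary research question, as to whether hesitant people have a lesser proportion of wish for vaccine advice". No covariate enters this test.
- **Measurements** and **Table 1** (under Data collection) show how much else the first survey holds: "confounding factors such as demographic data, health status of the parents and siblings, their vaccination status, and experience with vaccination will be assessed", and also "Type of information, source of vaccination information, influencing factors, and trustworthiness of information sources".
- **Sample size calculation** expects incomplete surveys: "Considering the possibility that some surveys could be incomplete, at least 400 parents are needed". The minimum before that allowance is 378.
- **Quality control** provides for direct clarification of incomplete responses with parents, and **Data collection** for up to five reminders to parents who do not answer a questionnaire.

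**The concern.** The rule asks for more than the primary analysis uses. A parent with a scoreable C7C and an answer on the wish for advice has everything the chi-square test needs. If that parent leaves a sibling's vaccination status or one trust rating blank, the literal rule removes the parent from a test that never looks at those items.

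The rule also works against the aim of its own paragraph, which takes care to keep parents who skip the second questionnaire and then sets a condition that can discard parents with intact primary data.

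Two things are at stake:

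- **Precision.** Under the planning assumptions, power depends mainly on the small number of hesitant parents, and the Discussion reports recruitment far below expectation.
- **Bias.** Several of the items that could be skipped concern vaccination, experience and trust. Completion could therefore be related to hesitancy and to interest in advice. Recruiting more parents protects the number analysed but does not correct selection.

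**Working it through.** **Inputs.** From Sample size calculation: wish for more information 4% in hesitant and 25% in non-hesitant parents; 7% hesitant; two-sided 5% level; 80% power; Fisher's exact test; minimum 378, raised to 400. Assumed, because the article gives no figure: the share of first surveys left incomplete, and how completion varies with hesitancy and the wish.

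**1. Reproduce the plan's figures.**

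Odds ratio = (0.25/0.75)/(0.04/0.96) = 8.0, as stated.

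Exact power = sum over x1 and x2 of Bin(x1; n1, 0.04) × Bin(x2; n2, 0.25), counting only tables with two-sided Fisher p ≤ 0.05.

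At N = 378, 7% is 26.5 hesitant parents:

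| Hesitant + non-hesitant | Fisher power |
|---|---|
| 26 + 352 | 79.2% |
| 27 + 351 | 81.0% |
| 28 + 350 (28 is the article's count) | 83.3% |

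The stated 80% is reproduced, so the sample size itself is not in question.

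**2. The plan's own allowance.** 1 − 378/400 = 22/400 = 5.5%. This rate is implied, not stated.

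**3. Power if incomplete first surveys are excluded from 400 recruited parents, with 7% hesitant.** Analysed N = 400 × (1 − d); hesitant = 7% of that, rounded. The last column is the normal-approximation power for the chi-square test that the Analysis plan names.

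| Excluded d | N | Hesitant + non-hesitant | Fisher | Chi-square approx. |
|---|---|---|---|---|
| 0% | 400 | 28 + 372 | 83.6% | 86.1% |
| 5.5% (plan) | 378 | 26 + 352 | 79.2% | 82.0% |
| 10% (assumed) | 360 | 25 + 335 | 76.0% | 79.4% |
| 15% (assumed) | 340 | 24 + 316 | 73.9% | 76.6% |
| 20% (assumed) | 320 | 22 + 298 | 70.1% | 70.5% |

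The 0% row shows what is kept if every incomplete survey still holds a scoreable C7C and a wish answer. Where the missing item is one of those two, no change of rule recovers the parent.

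**4. When exclusion biases the odds ratio.** Let c be the probability of completing the first survey in each cell. Then

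observed OR = true OR × [c(non-hesitant, wish)/c(non-hesitant, no wish)] ÷ [c(hesitant, wish)/c(hesitant, no wish)].

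With assumed completion rates:

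- Completion depends on hesitancy alone (70% hesitant, 95% non-hesitant): both ratios are 1, OR = 8.0.
- Completion depends on the wish alone, equally in both groups (95% with, 80% without): the ratios cancel, OR = 8.0.
- Hesitant 90% with the wish and 70% without, non-hesitant 95% throughout: OR = 8.0 × 1 ÷ (0.90/0.70) = 6.2.
- Non-hesitant 95% with the wish and 80% without, hesitant 95% throughout: OR = 8.0 × (0.95/0.80) ÷ 1 = 9.5.

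The odds ratio moves only under joint dependence, and it can move either way.

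**The case against.** **The sentence may mean less than it says.** It stands in a paragraph about attrition, where the contrast is between a first questionnaire that was answered and a second that was not. Answering completely could then mean no more than finishing and submitting. That reading is possible, but it is not what the words say, and an analyst who followed them would exclude item-level incompletes. The unseen SAP may define analysis sets in more detail, but the article has fixed a rule here and has not left the matter open.

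**The loss may be small and is partly budgeted.** Queries and reminders may recover some surveys, and the article does not say which items can be left blank. At the plan's own 5.5% allowance, power stays at about the planned level. This stands: the exclusion rates above 5.5% have no source in the article.

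**Hesitant parents may not be the scarce group.** A reader might infer from the table that the rule will leave the trial underpowered. The article does not support that. Its Discussion reports many more hesitant than non-hesitant participants so far. At an assumed 60:40 hesitant mix, excluding 15% of 400 leaves 204 + 136 and power near 100%. Exclusion would matter at that mix only if total recruitment stayed very low: 60 + 40 gives 85%, and 51 + 34 after 15% exclusion gives 77%.

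**Bias is not shown.** A reader might also infer that the rule selects on both exposure and outcome and so distorts the primary result. That needs joint dependence of completion on hesitancy and the wish, for which the article gives no evidence.

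**One denominator is convenient.** A single complete-case set keeps the primary test, regressions and four-group tables consistent. That is a genuine advantage, but a sensitivity analysis can provide it.

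**Conclusion.** The point holds in a limited form. As written, the inclusion rule is stricter than the primary analysis requires and would remove parents whose primary data are intact. That follows from the text alone and does not depend on the hesitant share.

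The size of the effect cannot be determined from the article. At the planned 7% share, power is about 79% at the plan's own allowance and about 76% to 74% if 10% to 15% of 400 are excluded. Those figures rest on assumed exclusion rates and do not carry over to the mix now being recruited. Selection bias is a risk that the larger target does not address; under assumed completion patterns the odds ratio of 8.0 could appear as 6.2 or 9.5, or not change at all. The change is worth making before analysis because it is simple and avoids both problems where the blank items are unrelated to the primary test.

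**What to change.** Replace the rule, in the protocol and the SAP, with a definition of the primary analysis set: all eligible, consenting parents with a scoreable C7C and a non-missing answer on the wish for advice at the first visit, whatever else is missing from the first survey and whether or not the second was answered.

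- Analyse secondary items on available data and report the denominator for each.
- Keep the set with a fully completed first survey as a sensitivity analysis of the primary test.
- Compare full with partial completers on attitude and wish, so that any selection becomes visible.

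If the intended meaning was only that the first survey had been submitted, the same sentence settles it. No new data are needed. The cost is one sentence in each document, a short additional table, and denominators that vary across secondary tables.

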## Discussion

This study addresses a very important population by clarifying whether vaccine-hesitant parents are generally less interested in vaccine advice (1). Furthermore, it can provide useful insight into the information wishes and needs of new parents. It is characterized not only by the fact that it deals with the population group most likely to come into contact with vaccinations, but also by the fact that it takes into account the three pillars of evidence-based medicine - science, patient and doctor - and their interactions, in this case from the parents’ perspective. These results can enhance information strategies, especially for new parents, and may give information on the different needs of vaccine-hesitant and non-hesitant parents.

However, this study has to deal with some difficulties, too. As research into vaccines continues to progress, the recommendations for childhood vaccinations are also constantly changing. This leads to parents being confronted with changing information, which may influence the comparability of the data. Particularly, the current recommendation for respiratory syncytial virus (RSV) vaccination in German newborns could influence the results, as the prospective study design cannot be realized for this vaccine if 3-day-old newborns receive vaccinations in the hospital before their first visit to a pediatrician (24). As the recommendation for those vaccinations depends on the month of birth, it may be necessary to include more families to be able to compare their strategies. On the other hand, there are legal and economic uncertainties with regard to the practical implementation of this recommendation, meaning that precise planning is not possible at the present time.

Another difficulty is finding participants for the study. Recruitment started in August 2023. Up to now, 42 parents have completed the second visit, the recruitment per month is far lower than expected, and the number of participating vaccine-hesitant parents is much higher than the non-hesitant parents. Therefore, the number of participating offices must be expanded, and the recruitment of non-hesitant parents needs to be optimized. By now, promotion strategies seem mostly to address vaccine-hesitant parents. Consequently, the wording and appearance of the flyer and other promotion materials will be designed with feedback from hesitant and non-hesitant parents. Other strategies could include multiplicators that give parents the possibility to register during their contact with the multiplicator or focusing on obstetric clinics as multiplicators. However, the current recruitment delay is due to initial organizational difficulties. We are currently working on eliminating these difficulties and developing advertisement strategies. We welcome further supporting offices, which is one of the reasons for submitting this protocol for publication.

Previous research has shown that balanced leaflets help to improve decision-making in parents and do not influence their decision (25). A more detailed understanding of the shared decision process, considering both the *a priori* and *a posteriori* wish for advice, the experienced advice, and vaccine administration as a common intervention, may help reduce vaccine hesitancy and improve public healthcare outcomes. Based on the findings of this study, an intervention that addresses parents’ needs for advice can be designed and tested. Furthermore, the results may help to secure resources in pediatric settings and improve vaccine acceptance if parents get the information they need. The findings about attitudes, interventions, and subsequent actions can be extrapolated to other medical settings such as medication, inpatient stays, or surgeries.

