The timing of the consultation could also play an important role, particularly in connection with childhood vaccinations. As immunization of infants is recommended as early as possible (16), one of the first decisions parents must take for their children after birth is whether they want to vaccinate as recommended or not, especially given that different countries have different recommendations. At no other time of life do humans face so many immunizations against as many pathogens as in the newborn phase and first year of life, on top of many other decisions, that this phase of family life requires. Hence, parents have to deal with much information at this time, and the vulnerable postpartum period can pose an extra strain on decision-making (16). Vaccinations are applied multiple times, but the most important is the first initial application, because parental experience of the first vaccinations may influence all following actions for their child (17). It is therefore particularly important to consider this phase of the first vaccination decision and make it as smooth as possible for the parents.

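### For infants given RSV immunisation in hospital at about 3 days, V1 does not precede the first immunisation; the exposure is not recorded at V1, and more families would not remove any bias

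*Protocol article*

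**What the plan says.** Data collection has registration and consent finish before the child's "first immunization, which is according to the immunization schedule as soon as the infant is 6 weeks old", and V1 is sent at 6 weeks. Primary study endpoint places the wish for advice before the first recommended vaccination period. Inclusion and exclusion criteria do not exclude an infant who has already been immunised. The Analysis plan forms two groups from the C7C alone and compares them by chi-square.

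The Discussion states that "the current recommendation for respiratory syncytial virus (RSV) vaccination in German newborns could influence the results", because "the prospective study design cannot be realized for this vaccine if 3-day-old newborns receive vaccinations in the hospital". It continues: "As the recommendation for those vaccinations depends on the month of birth, it may be necessary to include more families to be able to compare" the families' strategies. It adds that precise planning is not possible at present.

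The Introduction explains why the first dose matters: "parental experience of the first vaccinations may influence all following actions for their child".

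In Table 1 and under Measurements, the vaccination status taken at V1 is that of parents and siblings; the observed child's status appears only at V2. That V2 query "asks for the date, vaccine name, and diseases against which vaccinations are given" (Dealing with bias and limitations). The same section keeps parents without V2 in the primary analysis.

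**The concern.** The primary endpoint is meant to be the wish of parents who have not yet been through a vaccination of this child. For an infant immunised at about 3 days, the parents answer V1 some six weeks after a first decision and dose. By the protocol's own premise, that experience may influence what follows, for other vaccines as well as RSV.

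Three consequences follow:

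- **Primary comparison.** If prior immunisation is more common in one attitude group and also changes the wish for advice, the pooled comparison mixes the two effects. Hesitant parents may decline the dose. The planned redirection of promotion toward non-hesitant parents could also give the two groups different birth-month mixes.
- **Data.** What is not asked at V1 cannot be recovered for parents who never answer V2, whatever the analysis plan later specifies.
- **Action groups.** Secondary study endpoints does not name the vaccines that make a child immunised at 12 weeks. Read literally, an RSV dose given before attitude was measured would move a hesitant family that declined the later vaccines from group (c) to group (d). On the non-hesitant side it would move a family from (b) to (a).

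**Working it through.** **1. The plan's own figure.** Inputs from Sample size calculation: 4% vs 25%, 7% hesitant, Fisher's exact test, 80% power, two-sided 5%.

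- Odds ratio = (0.25/0.75)/(0.04/0.96) = 8.0, as stated.
- Exact Fisher power at a total of 378: 79.1% (26 vs 352), 81.0% (27 vs 351), 83.3% (28 vs 350).
- The figure of 378 reproduces, and this point does not affect it.

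**2. Timing.** A dose at about 3 days precedes V1 at 6 weeks. The premise of Data collection and Primary study endpoint therefore fails for each such child, for the primary endpoint as a whole.

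**3. When pooling biases the test.** Assume no attitude effect: 25% of unexposed parents in both groups wish for advice (odds 1/3). Prior immunisation halves the odds (1/6, so 14.3%) or doubles them (2/3, so 40%). Pooled rate = (1 - exposed share) x 25% + exposed share x 14.3% or 40%.

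| Exposed, hesitant vs non-hesitant | Odds | Hesitant | Non-hesitant | Spurious difference |
|---|---|---|---|---|
| 25% vs 50% | halved | 22.3% | 19.6% | +2.7 points |
| 25% vs 50% | doubled | 28.8% | 32.5% | -3.8 points |
| 25% vs 75% | halved | 22.3% | 17.0% | +5.4 points |
| 25% vs 75% | doubled | 28.8% | 36.3% | -7.5 points |

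Example, last row: hesitant 0.75 x 0.25 + 0.25 x 0.40 = 0.2875; non-hesitant 0.25 x 0.25 + 0.75 x 0.40 = 0.3625. With equal exposure the spurious difference is zero.

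**4. Error rates.** Simulation of 40,000 data sets, 28 vs 350, no attitude effect, two-sided 5%:

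| Exposed | Odds | Pooled chi-square | Mantel-Haenszel by prior immunisation |
|---|---|---|---|
| 50% vs 50% | halved / doubled | 4.6% / 4.6% | 4.8% / 4.9% |
| 25% vs 50% | halved / doubled | 7.2% / 5.7% | 4.9% / 4.8% |
| 25% vs 75% | halved / doubled | 13.3% / 11.1% | 4.7% / 5.1% |

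Stratifying costs little. At 4% vs 25%, with 50% exposed in both groups and no exposure effect, power is 86.5% stratified and 86.6% pooled.

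**5. Restriction to children not immunised before V1.** Equal exposure in both groups is assumed, with 378 enrolled:

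- 25% exposed: 21 vs 262, Fisher power 63%. Keeping 378 unexposed parents needs 378/0.75 = 504.
- 50% exposed: 14 vs 175, Fisher power 44%. Keeping 378 needs 378/0.50 = 756.

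**6. Action groups.** With 28 hesitant parents, each family reclassified from (c) to (d) shifts the split by 1/28 = 3.6 percentage points.

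**The case against.** The strongest reply is that the protocol already sees the problem. A reader might infer that it treats the damage as limited to RSV. It does not: only the design failure is tied to that vaccine, while the Discussion says that RSV could influence the results and that changing recommendations are something "which may influence the comparability of the data". The hospital timing is conditional, and the call for more families is tentative and aimed at comparing strategies. All of this stands.

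Stratified analyses and the coding of vaccination status are ordinary content for the analysis plan, which is not shown and may include them. That stands for the analyses, but not for the V1 data gap. Measurements does list experience with vaccination among the V1 confounders, but it is unclear whether this covers the observed child.

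Parents with older children also bring vaccination experience to V1, so mixed experience as such is not new. The point is confined to earlier immunisation of the observed child.

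A reader might also want RSV receipt as the primary stratifier. The question is descriptive, and receipt may follow from attitude, so conditioning on it could remove part of the association being asked about. Birth-month eligibility avoids that.

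Finally, the literal reading of immunised is not the only one. The 12-week visit is justified by the slot for the six-fold and rotavirus vaccines, and the four-group results are exploratory. The wording is ambiguous, not demonstrably wrong.

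**Conclusion.** The contradiction on timing is in the text and needs reconciling. As described, the child's exposure cannot be identified for parents with V1 only. More families would add precision or allow a comparison between families, but would not remove bias from pooling.

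No size of bias can be derived, because the documents give neither the share of infants immunised nor any effect on the wish. A reader might take an assumed 10-point fall in the wish, multiply it by an assumed 60% vs 20% exposure, and report 0.10 x 0.40 = 4 of the planned 21 points. That is unsupported, and a 10-point fall is impossible in a group with a 4% wish rate. The 6-13% type I error likewise rests on assumed exposure and odds.

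Nor is the primary test shown to be invalid. Under equal exposure its error rate stays nominal; bias requires exposure to differ by attitude, which is plausible but not documented. The direction is also open: with exposure less common in hesitant parents, a lower wish after the dose would mask the hypothesised difference, and a higher wish would inflate it.

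**What to change.** 1. Reconcile Data collection, Primary study endpoint and Discussion on what counts as the first immunisation and what V1 precedes.
2. Add one V1 item: whether and when the observed child has already been immunised, including against RSV.
3. Keep the pooled chi-square as the primary test. Prespecify two sensitivity analyses: a Mantel-Haenszel test stratified by birth-month eligibility or prior immunisation, and a restriction to children not immunised before V1. State that the restricted analysis has low power (about 63% at 25% exposed and 44% at 50%, both assumed).
4. Define the four action groups on vaccines whose recommended window falls between V1 and V2, and tabulate RSV separately.

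The cost is one question and two additional analyses. The downside is missing exposure for parents enrolled before the item is added who answer V1 only; V2 completers can be classified from the vaccination dates. Birth month should be available for all, since invitations run on the child's age. With 42 V2 completers reported against 378 needed (11%), an item added soon should still reach most of the sample, though the article does not give the number of V1 responses.
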